### Study Outcomes

#### Primary outcome

As a primary indicator, we consider AVF survival rate at 12 months and determined by the percentage of fistulas in use from the time-zero of study enrollment to the date of the first clinical intervention by angioplasty or vascular surgery, to maintain or restore patency – "unassisted patency" [15, 16].

To assess the variable "AVF survival" we consider the following criteria:- Fistula that is successfully cannulated with two needles, arterial and venous, that allows a prescribed blood flow of at least 300 mL/min and that allows for an adequate treatment will be considered a functioning AVF [17];- Fistula used without success will be considered a dysfunctional AVF, whether it has patency or not [15];- It will be considered AVF abandonment on the day that access is considered permanently unusable or not suitable for cannulation [17];

Referral for endovascular intervention [15, 16] will be based on two of the following factors of AVF dysfunction:- Decreased AVF blood flow (Qa) (assessed by thermodilution and <400 mL/min);- Increased hemostasis time (>10 min);- Cannulation failure: failure or inability to insert dialysis needles [17];- Decreased dialysis efficacy: low HD dose, *sp*Kt/V <1.2 [17] or substitution volume <21L. A parameter to quantify the HD adequacy (*sp*Kt/V) will be calculated based on ionic dialysance obtained by the integrated module Online Clearance Monitor (OCM®) from the 5008 CorDiax machine, and “*V*” was derived from total body composition assessment with a bioimpedance device (Body Composition Monitor - FMC) [18];

Or changes in the physical examination (changes in thrill, abnormal development of aneurysm, or progressive increase in edema in the AV limb) and plus one of the factors described above.

Referral for surgical intervention [15] will be based on one or more indicators of AVF dysfunction:- Rupture of the AVF wall;- AVF thrombosis;- Progressive development of aneurysm;- Acute bleeding: AVF bleeding requiring surgical intervention;- Local infection of the AVF;- Deficient distal perfusion with signs of ischemia.

### Secondary outcome

We will evaluate the assisted primary patency. As an outcome, we considered AVF survival rate at 12 month and determined by the percentage of fistulas in use from the time-zero the study enrolment, to the date of access abandonment due to dysfunction, patient abandonment, or death, treatment change modality or study end [15, 17, 19]. For the study, we will consider the frequency of interventions, both endovascular and surgical, to maintain functioning access [17].

We will also include the following secondary outcomes associated with cannulation:- Inflammation signs at the AVF cannulation site, defined by the presence of one or more signs: redness, edema or local exudate [4];- AVF local infection, defined by the presence of exudate at the cannulation site with a positive bacteriological culture;- Bacteremia related with AVF and confirmed with a positive blood culture (describe if swab was performed and/or infection treated with antibiotics);- Hematoma or infiltration: an incident that occurs during cannulation that can result in local infiltration, edema, or pain, which can be treated with local ice, but re-cannulation is possible [16];- Time to hemostasis: time to stop bleeding after needle removal, with up to 10 min considered normal [4];- Peri-needle bleeding: bleeding from the puncture site during treatment and requiring nursing intervention;- Aneurysm development: segment dilatation of the arterialized vein at three times the diameter of the segment considered normal, which means a segment with a width of ≥ 18 mm [20]. An increase in the existing aneurysm will be considered when the vein presents an increase in its diameter of ≥ 5 mm.- Local pain related to CT;- Presence of scab at the cannulation site;- Easy to identify cannulation site.

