**Methods:**

This MuST study is a multicenter, prospective, non-blind, parallel-group, randomized controlled trial with the intervention group submitted to MuST and a control group undergoing the rope-ladder, up to 100 subjects for each group. Patients will be randomized 1:1 to one of two cannulation technique (CT), and the follow-up period of this study will be 12 months. Primary outcome is to evaluate the arteriovenous fistula survival rate at 12 months determined by the percentage of fistulas in use from the beginning of the study to the date of the first clinical intervention by angioplasty or vascular surgery, to maintain or restore patency (unassisted patency). Secondary outcome is to evaluate arteriovenous fistula survival rate at 12 month determined by the percentage of fistulas in use from the study start to the date of access abandonment due to dysfunction, patient abandonment, or death, treatment change modality or study end. We will also evaluate the assisted primary patency and include the following secondary outcomes associated with the cannulation technique: Infection, Hematoma, Aneurysm development, and pain.

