The key VA person and the nurse’s team will be carried out the following steps:Collect AVF photo, before the start of the study (baseline), at 6 months and at 1 year during the study;MuST cannulation technique – select and identify cannulation sites with a dermographic pen until their location is easily visible due to skin depigmentation; Two areas of arterial and venous cannulation will be created, with three cannulation points each at least 1 cm apart;Rope-ladder cannulation technique – create a diagram of the cannulation sites’ orientation. The diagram will be attached to each patient’s dialysis file for quick reference;AVF physical examination before each HD treatment with recording of the findings;The daily results of each patient’s assessment will be recorded using the computer tool VASACC (vascular access) and on an Excel spreadsheet;The nurse who performs the cannulation will assess the intensity of pain perceived by the patient;Pain will be assessed immediately after cannulation of the arterial and venous area according to the 10 cm long visual analog scale (VAS) which has the classification “No Pain” on the far left and “Extreme Pain” on the right [4, 17, 21];Whenever there is a referral to the Vascular Access Center (VAC) for angiography or vascular surgery, a record will be made in the patient’s clinical file in the EUCLID database;After the intervention in the VAC, a record of the intervention per patient will be made in the Vascular Access OnLine database (AV OnLine). This registration will be performed by the nephrologist or vascular surgeon, depending on which intervention is performed. This information will then be transcribed into the Excel data collection Spreadsheet;Patients will be followed until access thrombosis, abandonment due to AVF dysfunction or surgical intervention with anastomosis alteration, patient abandonment from the study, transfer to another clinic, hospitalization, death, change of treatment modality or study end;For the variable pain intensity, time to hemostasis, peri-needle bleeding, Qa, dialysis dose (*sp*kt/V) and substitution volume will be evaluated at 3 time periods only: before study start, at 6 months, and at 12 months;Presence of scab at the cannulation site and the ease of identifying the cannulation site will be evaluated at the same time periods, but only for CT MuST;Monthly meetings will be held with the head nurse and key VA person, and additional meetings whenever necessary. All situations deviating from normality there will be discussed. Verification and collection of data.

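### The secondary access-survival outcome is inconsistently defined: no split of failures from censoring, follow-up that stops at thrombosis, and a label used in two ways

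*Protocol article*

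**What the plan says.** Five places in the protocol article bear on this outcome.

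- **Secondary outcome.** The section opens "We will evaluate the assisted primary patency" and sets the outcome as "AVF survival rate at 12 month and determined by the percentage of fistulas in use from the time-zero the study enrolment", running "to the date of access abandonment due to dysfunction, patient abandonment, or death, treatment change modality or study end". It adds that the frequency of endovascular and surgical interventions will be considered.
- **Intervention (follow-up rule).** "Patients will be followed until access thrombosis, abandonment due to AVF dysfunction or surgical intervention with anastomosis alteration", and further "patient abandonment from the study, transfer to another clinic, hospitalization, death, change of treatment modality or study end".
- **Primary outcome.** "Referral for surgical intervention [15] will be based on one or more indicators of AVF dysfunction:- Rupture of the AVF wall;- AVF thrombosis" begins the list of surgical indications. The same section defines abandonment as the day the access is judged permanently unusable or unfit for needling. It describes interventions as intended to maintain or restore patency.
- **Abstract, Methods.** The abstract gives the same end-date list as the secondary outcome and then adds: "We will also evaluate the assisted primary patency".
- **Statistical analysis.** Analysis is by intention to treat. Kaplan-Meier curves are named for the primary outcome only. Study withdrawal stands in the same phrase as the event and is not called censoring.

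**The concern.** A survival outcome needs a failure event, a rule for every other exit, and follow-up that reaches the event. Here the failure event is not separated from the other exits, and follow-up can stop before abandonment is reached. The label also does not settle which patency is meant.

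If deaths and modality changes with a working fistula are counted as losses, events that there is little reason to link to cannulation technique enter both arms and pull the comparison toward no difference. If thrombosis ends follow-up, the analyst must either call it a failure or censor it, and each choice measures something other than time to permanent abandonment. In an unblinded trial, leaving these choices open allows them to be made after the results are visible. The Discussion names assisted primary patency among the things the previous trial did not evaluate and this one will, so it is part of the stated rationale.

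**Working it through.** The document states no rate, power or effect for this outcome, so there is no figure to reproduce. The check is a comparison of sections, followed by illustrations on assumed rates.

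**Step 1. Compare the two lists of exits.**

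| Exit | Ends the secondary outcome | Ends follow-up (Intervention) |
|---|---|---|
| Abandonment for dysfunction | yes | yes |
| Thrombosis | not listed | yes |
| Surgery altering the anastomosis | not listed | yes |
| Hospitalization | not listed | yes |
| Transfer to another clinic | not listed | yes |
| Patient abandonment | yes | yes |
| Death | yes | yes |
| Modality change | yes | yes |
| Study end | yes | yes |

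Four exits stop follow-up but do not end the outcome. Of the five that end the outcome, only the first is access loss.

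**Step 2. Two readings of the list.** The primary outcome uses the same construction: the share of fistulas in use from time zero to a date, where that date is the failure (first intervention). Read in parallel, every item in the secondary list is a failure. Read like the follow-up rule, the items are ends of observation, and only abandonment for dysfunction is a failure. The Statistical analysis section does not choose between them.

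**Step 3. Thrombosis.** Thrombosis is an indication for surgery and abandonment is permanent loss, so a clotted fistula may be restored and used again. Follow-up has by then stopped. Its time to abandonment is unobserved, and so are its later interventions, which the Secondary outcome section also wants counted.

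**Step 4. Illustration of the failure reading (all rates assumed, constant hazards).** Let a be the control hazard of access loss, o the hazard of other exits (equal in both arms), and HR the true hazard ratio for access loss.

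Composite hazard ratio = (a × HR + o) / (a + o), with a = 0.08 per year and HR = 0.50:

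- o = 0.10: (0.04 + 0.10) / 0.18 = 0.78. Non-access share of failures 0.10 / 0.18 = 56%. Control 12-month survival exp(−0.18) = 83.5%.
- o = 0.15: (0.04 + 0.15) / 0.23 = 0.83. Non-access share 0.15 / 0.23 = 65%. Control survival exp(−0.23) = 79.5%.
- Access loss alone: exp(−0.08) = 92.3%.

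On the percentage scale, composite survival = access survival × (1 − q), where q is the 12-month share leaving for other reasons. With assumed access survival of 80% versus 90%:

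- q = 10%: 72% versus 81%, difference 9 points.
- q = 20%: 64% versus 72%, difference 8 points.
- q = 30%: 56% versus 63%, difference 7 points.

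**Step 5. Illustration of the thrombosis conflict (rates assumed).** Take 12-month risks of 5% for non-thrombotic abandonment and 10% for thrombosis, with a share s = 50% of thromboses salvaged for the rest of the year. Hazards are hA = −ln(0.95) = 0.0513 and hT = −ln(0.90) = 0.1054.

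- Every thrombosis a failure: exp(−(hA + hT)) = 85.5%.
- Thrombosis censored: exp(−hA) = 95.0%.
- True survival to abandonment: exp(−(hA + hT × (1 − s))) = exp(−0.1040) = 90.1%.

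With thrombosis risk at 5% the two computable versions are 90.2% and 95.0%; at 15% they are 80.7% and 95.0%. The gap runs from about 5 to about 14 points.

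**The case against.** The strongest reply is that the list cannot be a list of failures. It includes study end, and if study end were a failure, survival would be 0% in both arms. The follow-up rule uses a nearly parallel list plainly as ends of observation. A journal article may also leave the failure and censoring split to an analysis plan that is not shown. This has force. A reader might infer that the outcome, as written, does not measure fistula survival; the document does not support that, because on the end-of-observation reading it gives a conventional access-survival curve. The dilution in Step 4 applies only to the other reading and rests on assumed hazards.

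A reader might also infer that the outcome cannot be computed. That too goes further than the text. It is unaffected by the thrombosis rule for every fistula that does not thrombose. For the rest it can be computed once thrombosis is counted as a failure or censored. Stopping at thrombosis even suits an assisted-patency outcome that ends at first thrombosis. The only quantity the thrombosis rule puts out of reach is time to abandonment after a salvaged thrombosis.

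Two defects do not depend on a missing analysis plan. The follow-up rule and the outcome's end points disagree on four exits. The abstract separates what the Secondary outcome section treats as one. Both are contradictions in the text shown.

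**Conclusion.** The point holds as an inconsistency of definition, of moderate severity. The list permits two readings that give different results. The follow-up rule leaves the stated end point unobserved after a salvaged thrombosis. Assisted primary patency is a separate outcome in the abstract and the same outcome in the body. Ending observation at hospitalization or transfer also sits badly with the intention-to-treat statement.

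The size cannot be fixed from the document. On the assumed rates above, counting non-access exits as failures moves a hazard ratio of 0.50 to between 0.78 and 0.83, or shrinks a 10-point difference to between 7 and 9 points. The handling of thrombosis moves the 12-month estimate by about 5 to 14 points. These figures show that the choices matter; they do not show which one the investigators intend. The primary outcome, unassisted patency to first intervention, does not use this definition.

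**What to change.** Reconcile the abstract, the follow-up rule under Intervention, and the Secondary outcome section before any comparison by arm is made.

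1. Define assisted primary patency as time from enrolment to first thrombosis or abandonment for dysfunction, whichever comes first, and use that name for nothing else. The present follow-up rule already runs to both events.
2. Count only access loss, as so defined, as failure. Treat death and modality change as competing events, or censor them in a cause-specific analysis. Treat withdrawal, transfer and study end as censoring.
3. State how hospitalization and anastomosis-altering surgery are classified. Hospitalization deserves thought, because the Background names vascular access as one of its main causes, so censoring there may not be independent of the outcome.
4. Report survival to permanent abandonment as a separate outcome only if access status is recorded after thrombosis, for example from the intervention and clinical databases already in use.

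Items 1 to 3 are changes of wording and use data already collected. Item 4 costs added data collection, and status after thrombosis may be hard to recover if it is not recorded at the time.

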### Outcome parameters

For the sample characterization, we will describe the sociodemographic characteristics, comorbidities and laboratory data immediately before the start of the study (baseline). We will also describe the interventions already carried out in active AVF within the last year (T0).

### Data collection instrument

To collect the data, an Excel Spreadsheet was created, consisting of 5 sheets:

Patient baseline; Follow-up data changes; Follow-up data semester; AVF intervention and Outcome.The data resulting from the evaluations will be collected from the VASACC and EuCliD databases and recorded on the Excel data collection Spreadsheet.A computer file will be created to store the patient’s VA photos. Each photo will be given an identification number.

### Data usage

The use of the information collected is exclusively for academic purposes and the results of the study may be published in peer-reviewed scientific journals and presented at relevant national and international meetings, preserving the identity of all participants

Pain assessment scale:Visual analog scale (VAS).

Pain will be assessed immediately after cannulation of the arterial and venous area according to the 10 cm long visual analog scale (VAS) which has the classification “No Pain” on the far left and “Extreme Pain” on the right [4, 17, 21].

The values obtained will later be registered on the Excel data collection Spreadsheet.

### Statistical analysis

Data will be analyzed according to the “intention-to-treat” [15]. The continuous variables of the “baseline” will be expressed through measures of location, dispersion and the categorial variables will be summarized using absolute and relative frequencies. Descriptive comparisons and tests will be performed between groups at baseline, at 6 and 12 months. To compare two groups by continuous variables, parametric tests will be used, namely the t-test, or nonparametric tests if normality is not assumed.

To analyse relationship between categorical variables, the Chi-square test (χ^2^) will be conducted, or Fisher’s exact test when appropriate.

The primary factors to assess fistula survival will be calculated over time from baseline to time requiring intervention (no patency assistance) or withdrawal from the study. In this case we will use the Kaplan–Meier survival curves.

For secondary factors, such as the frequency of hematoma, signs of infection, local infection or bacteremia, and thrombosis, the number of events per 1000 days of AVF will be calculated [16].

Results will be considered significant when *p* < 0.05. All the statistical analysis will be performed using SPSS (version 23; IBM, Armonk, NY, USA).

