### Study hypotheses

This study examines the following hypotheses:- Does MuST allow 10% rate of greater AVF survival in patients on a regular HD program in private HD clinics than RL?- Does MuST have a lower AVF complication rate in patients on a regular HD program in private HD clinics than RL?- Do patients submitted to MuST perceive less pain than patients submitted to RL?

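### Pain and the other continuous secondary outcomes are measured at baseline but compared by tests that ignore the baseline value; adjusting for it would gain precision at no cost in data.

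*Protocol article*

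**What the plan says.** The Intervention section of the protocol article sets the schedule. It begins "For the variable pain intensity, time to hemostasis, peri-needle bleeding, Qa, dialysis dose", adds substitution volume, and states that these "will be evaluated at 3 time periods only: before study start, at 6 months, and at 12 months". Each of these outcomes therefore has a pre-study value for the same patient.

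The Statistical analysis section sets the comparison: "Descriptive comparisons and tests will be performed between groups at baseline, at 6 and 12 months". For continuous variables, "parametric tests will be used, namely the t-test, or nonparametric tests if normality is not assumed". It names no covariate, change score or repeated-measures model.

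Pain carries more weight than the other secondary outcomes because it is the third study hypothesis: "Do patients submitted to MuST perceive less pain than patients submitted to RL". The section on recruitment says the groups are stratified by diabetes and AVF vintage. The Statistical analysis section gives neither factor a role.

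**The concern.** A two-group t-test or rank test at a visit sees only the values from that visit. The baseline measurement, often a good predictor of the same patient's later value, does no work in the comparison. Two things follow.

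- **Precision.** Between-patient variation that baseline could explain stays in the error term. The confidence interval is wider than it need be, and any chance imbalance at baseline passes into the estimated difference.
- **The baseline test.** The one inferential use made of baseline is a test between the groups. Under randomisation any baseline difference is due to chance, so the p-value answers no question that the trial asks.

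What is at stake is the sharpness of the answer on pain, Qa, dialysis dose, substitution volume and hemostasis time. The validity of that answer is not in question.

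**Working it through.** The article gives no standard deviation, target difference or power for these outcomes, so there is no figure of its own to reproduce. What follows is illustrative.

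**Inputs from the article**
- Up to 100 patients per arm, 1:1 (Methods).
- Significance at p < 0.05 (Statistical analysis). Sidedness is not stated; two-sided is assumed.

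**Assumptions not in the article**
- Correlation r between baseline and follow-up: 0.2 to 0.7.
- For the power column, a true difference of 0.4 SD.

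**Formulas**
- Variance of the arm difference, unadjusted: 2·SD²/n. Adjusted for baseline: 2·SD²·(1 − r²)/n.
- Equivalent sample size multiplier: 1/(1 − r²).
- Minimum detectable difference at 80% power: (1.960 + 0.842)·SD·√(2(1 − r²)/n).
- Power at 0.4 SD: Φ(0.4/√(2(1 − r²)/n) − 1.960).

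**Results with n = 100 per arm**

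| r | Variance factor 1 − r² | Equivalent to this multiple of the patients | Detectable difference (SD) | Power at 0.4 SD |
|---|---|---|---|---|
| unadjusted | 1.00 | 1.00 | 0.396 | 81% |
| 0.2 | 0.96 | 1.04 | 0.388 | 82% |
| 0.3 | 0.91 | 1.10 | 0.378 | 84% |
| 0.5 | 0.75 | 1.33 | 0.343 | 90% |
| 0.7 | 0.51 | 1.96 | 0.283 | 98% |

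For example, at r = 0.5 the detectable difference is 2.802 × √(2 × 0.75/100) = 2.802 × 0.1225 = 0.343 SD.

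**Check by simulation** (3,000 trials per setting, 100 per arm, true difference 0.4 SD). The t-test gave 80% to 81% power. The baseline-adjusted analysis gave 85%, 90% and 98% at r = 0.3, 0.5 and 0.7, in line with the table.

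**With fewer patients measured at 12 months.** If 20% had no 12-month value (an assumption), 80 per arm remain. Power at 0.4 SD is then 72% unadjusted, and 73%, 76%, 83% and 94% adjusted at r = 0.2, 0.3, 0.5 and 0.7. The adjustment works on the patients who are measured. It does not bring back those who are not.

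The further gain from adjusting for diabetes and AVF vintage cannot be sized from the article.

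**The case against.** **The unadjusted test is not an error.** This stands. With 1:1 randomisation a t-test or rank test at a visit controls its type I error, and nothing in the Statistical analysis section is false. The point is a better method using data already scheduled. An unseen analysis plan could add detail, but the article itself names the tests, and a baseline-adjusted analysis would replace them.

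**The gain may be small.** This also stands. Baseline pain is recorded under whatever technique the fistula had before, and follow-up up to a year later under the assigned one. A low r is plausible, and at r = 0.2 the gain is only 4%.

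A reader might also infer stronger criticisms that the documents do not support:

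- **That 12-month values come only from fistulas that have not failed, and that a repeated-measures model would cure this.** Follow-up does stop at several fistula-related events: "Patients will be followed until access thrombosis, abandonment due to AVF dysfunction or surgical intervention with anastomosis alteration, patient abandonment from the study", followed by further reasons. Angioplasty is not on that list although it counts as a primary event, so fistulas treated that way stay in the comparison. Nor is a model a cure. With baseline as a covariate it still omits patients who leave before 6 months. It also assumes missing at random, which is doubtful when exit is linked to dysfunction. Once a fistula is abandoned, its Qa and cannulation pain no longer exist.
- **That two visits give a 9.8% false-positive rate for the pain hypothesis.** The figure 1 − 0.95² = 0.0975 needs independent visits. The same patients are measured twice; with an assumed correlation of 0.4 to 0.7 between the test statistics the rate is 9.3% to 8.3%. Which visit decides is commonly left to the analysis plan, so its absence here is not a fault.
- **That the unmasked nurse scores the pain.** The article says "The nurse who performs the cannulation will assess the intensity of pain perceived by the patient" but does not say who marks the visual analog scale. The patient may do so, and the patient is unmasked as well. It openly states that neither can be blinded.

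**Conclusion.** The point holds as a free improvement to the analysis of secondary outcomes. The named tests are valid but leave unused a baseline value collected for every one of these outcomes, along with the two stratification factors. The baseline significance tests are uninformative.

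The size depends wholly on r. Over 0.2 to 0.7 the unadjusted comparison needs about 1.04 to 1.96 times the patients for the same precision. This range is an assumption: the lower end would be barely noticeable, while the upper end would matter for the pain hypothesis. Adjustment does not solve early exit, and the primary Kaplan–Meier analysis is not affected.

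**What to change.** In the Statistical analysis section, replace the visit-wise tests for pain VAS, Qa, spKt/V, substitution volume and time to hemostasis with a baseline-adjusted model:

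- Use either ANCOVA at 12 months or a mixed model for repeated measures with arm, visit and arm × visit. Include the baseline value, diabetes and AVF vintage in both.
- Report the 12-month arm difference with its 95% CI as the main contrast for each outcome.
- If residuals are clearly non-normal, as may happen with VAS scores and hemostasis times, use a transformation or rank-based ANCOVA. This takes the place of the present nonparametric fallback.
- Keep the descriptive baseline table and drop significance tests at baseline.
- State that the results apply to fistulas still in use, and that the mixed model, if used, assumes missing at random.

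The cost is a few sentences of wording. No new measurement, visit or staff is needed, because the baseline values are already scheduled and the stratification factors must be known at randomisation.

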### Study population

#### Recruitment of the study population

Patients with end-stage kidney disease (ESKD) on a regular HD program will be recruited in 3 private dialysis clinics operating in Portugal. Decision on a study participation is made by the patient. The treading physician will inform the patient about the study and provides written information. If the patient is not willing to participate in the study by giving its written informed consent, the patient cannot be included in the study.

The patients who signed the informed consent and meet the inclusion and exclusion criteria, will be randomly organized into two groups – intervention and control groups. Each group will be stratified according to the following criteria: diabetes and AVF vintage to ensure that these variables is properly represented in the sample and avoid bias*.*

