#### Inclusion criteria

Patients with AVF will be selected when:Are on a regular HD program with three weekly sessions;AVF has been in use for at least 8 weeks without incident;AVF with blood flow (Qa) ≥ 500 mL/min evaluated by thermodilution;AVF paths allow cannulations along the entire length of the vein with at least 6 cm of distance between bevels, or two distinct areas of 3 cm in length;Adult patients

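### Randomised groups are to be significance-tested at baseline, while baseline Qa, already measured and linked to the primary event, has no part in the stated primary analysis

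*Protocol article*

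**What the plan says.** **Baseline testing.** The Statistical analysis section states "Descriptive comparisons and tests will be performed between groups at baseline, at 6 and 12 months". For continuous variables "parametric tests will be used, namely the t-test, or nonparametric tests if normality is not assumed"; categorical variables get chi-square or Fisher's exact tests. The criterion is "Results will be considered significant when *p* < 0.05", with no exemption for baseline.

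**Primary analysis.** Fistula survival is to run from baseline to intervention or withdrawal, and "In this case we will use the Kaplan–Meier survival curves". The article names no model or covariate.

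**Qa.** It is an entry criterion: "AVF with blood flow (Qa) ≥ 500 mL/min evaluated by thermodilution" (Inclusion criteria). The Intervention section schedules it before study start, at 6 months and at 12 months. It is also a listed factor for endovascular referral: "Decreased AVF blood flow (Qa) (assessed by thermodilution and <400 mL/min" (Primary outcome). That referral "will be based on two of the following factors of AVF dysfunction", or on a changed physical examination plus one such factor. The surgical list does not include Qa.

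**Stratification.** "Each group will be stratified according to the following criteria: diabetes and AVF vintage" (Recruitment of the study population). Qa is not a stratification factor.

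**The concern.** A test between randomised groups at baseline asks whether the difference arose by chance, when randomisation already answers that it did. It can mislead in two ways. A small p-value looks like a fault in the allocation and invites adjustment chosen after seeing the data. A large p-value looks like reassurance, although an imbalance in a strong predictor can matter well below the significance threshold.

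Qa is where this could matter most. The primary event is the first angioplasty or surgery to maintain or restore patency, and low Qa counts toward the decision to refer. A fistula that starts near the entry limit is closer to the referral value than one that starts high. The design does not balance the arms on Qa, and the stated primary analysis does not correct for it. At stake is how well the trial uses a measurement it already has, not whether its primary comparison is valid.

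**Working it through.** The article gives no power, control rate, event count or prognostic strength for Qa, so there is no figure of its own to reproduce. All sizes below are illustrations on stated assumptions.

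**1. Chance findings among baseline tests.** With k independent tests at 0.05, P(at least one p < 0.05) = 1 − 0.95^k. The article does not give k; the Outcome parameters section lists sociodemographic, comorbidity, laboratory and prior-intervention data.

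| k (assumed) | P(at least one) |
|---|---|
| 5 | 0.23 |
| 10 | 0.40 |
| 15 | 0.54 |
| 20 | 0.64 |

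**2. What a non-significant baseline test can hide.** With 100 per arm (the planned maximum), the standard error of a difference in means is √(2/100) = 0.141 SD. A difference of up to 1.96 × 0.141 = 0.28 SD would pass. To first order, an imbalance of d SD shifts the treatment log hazard ratio by β × d, where β is the log hazard ratio per SD of lower Qa. For scale, take 12-month intervention rates of 25% v 15% (assumed; the 10-point gap follows the Study hypotheses). The log hazard ratio is then ln[ln 0.85 / ln 0.75] = −0.57.

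| β (assumed) | Hazard ratio per SD | Shift = β × 0.277 | Share of 0.57 |
|---|---|---|---|
| 0.4 | 1.49 | 0.11 | 19% |
| 0.7 | 2.01 | 0.19 | 34% |
| 1.0 | 2.72 | 0.28 | 49% |

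These are near-worst cases among imbalances that would pass the test. They show that p > 0.05 is the wrong yardstick; they are not the expected shift, which is zero under randomisation.

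**3. Distance from entry to the Qa referral value.** From 500 mL/min: (500 − 400)/500 = 20% fall. From 1000 mL/min (an example value): (1000 − 400)/1000 = 60% fall. This is the distance to one contributing factor, not to the event.

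**4. Gain from adjusting for Qa.** Two sets of simulated trials, 100 per arm, compared a Cox model with treatment alone against treatment plus standardised baseline Qa.

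Set A: 25% v 15% intervention, about 14% loss, 1500 runs per setting (Monte Carlo standard error about 1.3 points).

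| β | Power without Qa | Power with Qa | Gain (points) |
|---|---|---|---|
| 0.4 | 0.362 | 0.375 | 1.3 |
| 0.7 | 0.405 | 0.447 | 4.2 |
| 1.0 | 0.400 | 0.481 | 8.1 |

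Set B: no loss, 10-point difference, 800 runs per setting (standard error about √(0.4 × 0.6/800) = 1.7 points).

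| Control patency | Hazard ratio per SD | Power without Qa | Power with Qa |
|---|---|---|---|
| 0.60 | 1.0 | 0.282 | 0.285 |
| 0.60 | 1.25 | 0.301 | 0.306 |
| 0.60 | 1.5 | 0.302 | 0.328 |
| 0.60 | 2.0 | 0.292 | 0.329 |
| 0.75 | 1.0 | 0.400 | 0.398 |
| 0.75 | 1.25 | 0.410 | 0.422 |
| 0.75 | 1.5 | 0.404 | 0.422 |
| 0.75 | 2.0 | 0.401 | 0.444 |

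Set B gains about 0 to 4 points. As a check, the two-proportion formula for 75% v 85% patency with 100 per arm gives power 0.42, close to the simulated 0.40. Taken together, the gain is about 0 to 8 points; the top of that range needs a hazard ratio of 2.7 per SD. Neither set includes the stratification factors.

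**The case against.** The strongest reply is that the article condenses a fuller protocol, that covariate choice is normally settled there or in the SAP, and that an unadjusted comparison of randomised arms is valid. That stands. The Qa part is an improvement available from data in hand, not an error in the plan.

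A reader might infer several stronger things that the article does not support:

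- *That low Qa by itself produces a primary event.* It does not. Endovascular referral needs a second factor or an examination change, and Qa is absent from the surgical list. Scheduled Qa evaluations are also few, and the last falls at the end of follow-up.
- *That the primary comparison is biased without Qa.* It is not, over repeated randomisations. A given allocation can be unbalanced by chance, and adjustment addresses that.
- *That baseline tests will decide the adjustment.* No section makes any analysis depend on a baseline p-value. This is a risk that the tests create, not a stated plan.
- *That testing uses up the baseline data.* Qa remains fully usable afterwards.

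The reply also notes that the gain is modest and rests on assumed prognostic strengths, and that adjustment is not entirely free, because a Cox hazard ratio then becomes conditional on the covariates. Both are right. It adds that the stratification factors have a claim to be in the model from the article's own text; they belong in the fix beside Qa.

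What the reply does not remove is the planned baseline testing, which is stated outright.

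**Conclusion.** The point holds in a limited form. Baseline significance testing is planned and is uninformative if randomisation is sound. Removing it changes no primary estimate, error rate or sample size; it removes a source of misreading whose chance of at least one false alarm is 40% to 64% with 10 to 20 independent variables.

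The stated primary analysis is valid but makes no use of a baseline measurement that every patient has and that contributes to referral for the primary event. Prespecified adjustment would correct chance imbalance in Qa and add about 0 to 8 points of power. That range rests on assumed control patency of 0.60 or 0.75, a 10-point difference, 100 per arm and a hazard ratio per SD of lower Qa between 1.0 and 2.7. If Qa predicts intervention weakly, the gain is negligible.

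**What to change.** In the Statistical analysis section:

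1. Limit baseline to description by group (location, dispersion, frequencies) and remove significance testing at that time point. Tests at 6 and 12 months are not affected.
2. Keep the Kaplan–Meier curves by arm for display.
3. Prespecify a Cox model for time from baseline to first intervention, with treatment, baseline Qa as a continuous variable, diabetes and AVF vintage, whatever balance is observed. Fix the scale of Qa and the coding of vintage in advance.
4. Report the unadjusted hazard ratio alongside, because the adjusted one is conditional on the covariates and the two need not coincide even with perfect balance.

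Keep the covariate list this short. Under the assumed 25% v 15% there would be about 100 × 0.25 + 100 × 0.15 = 40 events before loss, or about 10 per coefficient if diabetes and vintage each take one.

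The cost is wording, settled before outcome data are examined. Qa is already measured for eligibility, and the stratification factors must be known at randomisation, so no new data are needed.
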